### Reference Standard

The reference standard is WB-MRI, which is comprised of conventional MRI sequences combined with WB-MRI diffusion acquisition. Each FL found on 18F-choline or 18-FDG PET/CT and not present on MRI will undergo multidisciplinary consensus between hematologists, nuclear medicine physicians, and radiology physicians. A decision will be reached and will classify an FL as a true-positive or false-positive finding based on patient charts and results from 18-FDG PET/CT, 18F-choline PET/CT, and WB-MRI at baseline but also based on lesion response to chemotherapy during a 12-month follow-up.

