## Methods

The scheme of the current prospective trial is shown in Figure 1, and the trial is described hereafter. Within a 21-day period, patients undergo 3 imaging procedures in the following order: 18F-choline PET/CT, 18-FDG PET/CT, and WB-MRI. The second and third imaging procedures will be performed 7 days ± 7 days from the previous procedure.

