#### Interpretation Criteria

After anonymization, images will be independently read by two experienced nuclear medicine physicians, blinded from clinical data, biological data, and other imaging data performed during the protocol.

18F-choline has physiological uptake by the liver, spleen, pancreas, salivary glands, and urinary tract. Lymph node uptake will not necessarily be considered pathological, particularly in the mediastinum, as lymphadenitis and granulomatosis are sources of false positive findings. Any focal bone uptake will be considered pathological if the uptake is superior to that of surrounding background activity. The following 6 skeletal areas will be defined: skull, sternum-ribs, spine, pelvis, superior limbs, and inferior limbs. The number of focal lesions (FL), localization, and intensity of uptake (SUVmax) will be described for each skeletal area. Diffuse infiltration of the spine will be defined as diffuse spine uptake that is superior to liver uptake [11,14].

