#### Interpretation Criteria

After anonymization, MRI images will be reviewed by two experienced radiologists blinded from PET/CT, clinical, and biological data. An FL is defined on coronal and sagittal sequences as a lesion with a diameter of more than 5 mm, with a low signal intensity on T1-weighted imaging and a high signal intensity on T2-weighted imaging. On DW images, an FL is defined as focal intensity above the bone marrow background signal. Diffuse bone marrow infiltration is defined based on previously published criteria [21]: a vertebral body to vertebral disk signal ratio <1.3 on T1-weighted images, vertebral body to psoas muscle signal ratio >2 on T2-weighted images, and vertebral body to kidney signal ratio >1 on DW images. A mild infiltration is defined as a pathological finding on T2-weighted or DW sequences. A moderate infiltration is defined as a pathological finding on both T2-weighted and DW images; a severe infiltration is defined as a pathological finding on both aforementioned sequences and on T1-weighted images.

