### Primary Outcome Measures

#### Number of Whole-Body Bone Lesions on 18F-Choline PET/CT and 18-FDG PET/CT

Every bone lesion will be validated using the reference standard, which is WB-MRI. A bone lesion that is not present on MRI but is present on any of the PET modalities must be validated by an expert multidisciplinary consensus.

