### Sample Size Calculation and Statistics

The main objective is to compare the number of FL detected on 18F-choline PET/CT and 18-FDG PET/CT, after confirming that each lesion exists on the reference standard. Data from a recent article showed that 18F-choline detects 75% more bone lesions than 18-FDG PET/CT [22]. Intrapatient concordance was 0.85. For each tracer, the standard error and mean of the distribution of the number of lesions wsere equal. We hypothesized that we will observe an average number of 10 bone lesions on 18-FDG PET/CT and that this number will increase by 75% on 18F-choline.

With a type I error of 5% and power of 90%, it will be necessary to include 23 patients. Due to the probability that the number of lesions will not follow a normal distribution, we will use a Wilcoxon signed-rank test, which is less powerful than the Student *t* test. To compensate for this lack of power, we will include 30 patients.

The secondary objectives are to compare the global accuracy of 18F-choline PET/CT and 18-FDG PET/CT as well as the accuracy of these two modalities in each of the 6 skeletal areas defined earlier for the detection of MM bone lesions. Accuracies of each modality will be compared using the McNemar test. Other secondary objectives will include the comparison of the accuracies of 18F-choline PET/CT and 18-FDG PET/CT for detecting diffuse infiltration of the spine using the McNemar test. Comparison of the number of extramedullary lesions detected by 18-FDG PET/CT and 18F-choline PET/CT will be performed using the Wilcoxon signed-rank test.

Interobserver and intraobserver agreements of PET/CT readings will be evaluated using the Cohen kappa coefficient.

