## Discussion

### Overview

A recent study showed that the rate of false-negative results for 18-FDG PET/CT for the detection of bone disease in MM is about 10%, which could be attributed to a lower expression of hexokinase 2 [13]. A more sensitive tracer is therefore needed.

The role of 18F-choline in the management of relapsed prostate cancer is well-established, and it also has a role in the characterization of hepatocellular carcinoma. However, it remains poorly explored in the field of hematological diseases. 18F-choline is incorporated into the membrane of cells in division and could reflect the higher rate of neoplastic plasma cells.

A recent retrospective study has shown that 18F-choline detects 75% more focal bone uptakes than 18-FDG PET/CT [18]. However, this study was performed on a heterogeneous previously treated population with suspected progressive disease or relapse. It is known that 18-FDG metabolism in myeloma cells can change after first-line treatment and that FDG-negative myeloma cases at diagnosis can turn FDG-positive when they relapse [13].

This prospective comparative study of diagnostic accuracies will evaluate if 18F-choline PET/CT is superior to 18-FDG PET/CT in a homogenous population with de novo MM. The expected role (according to STARD 2015 definitions) of 18F-choline PET/CT is the replacement of 18-FDG PET/CT. The study has been designed to comply with QUADAS 2 guidelines. We will carefully exclude patients that are already being treated with corticosteroids because of the increased risk of false-negative findings on 18-FDG PET/CT and patients that had a recent injection of bone marrow stimulation factors because of the risk of a false-positive assessment of bone marrow on PET/CT and MRI [14]. Also, 18-FDG PET/CT, 18F-choline, and WB-MRI will be performed within a short time period to avoid misinterpretation due to the apparition of new bone lesions during the protocol.

By analyzing the number of bone lesions per skeletal area, we expect to find that 18F-choline is superior to 18-FDG PET/CT for the detection of bone lesions, especially in the skull, as 18F-choline has no brain uptake. A previous study showed that the median uptake of 18F-choline is higher than that of 18-FDG [18]. Hence, we expect that 18F-choline PET/CT will be more sensitive than 18-FDG PET/CT for the detection of focal bone lesions as well as for the detection of diffuse infiltration.

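### PET-positive, MRI-negative foci enter the primary lesion count through a consensus that uses the two PET scans being compared

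*Protocol article*

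**What the plan says.** The sample size section of the protocol article sets the primary aim: "The main objective is to compare the number of FL detected on 18F-choline PET/CT and 18-FDG PET/CT, after confirming that each lesion exists on the" (the sentence ends by naming the reference standard). The primary outcome section adds: "Every bone lesion will be validated using the reference standard, which is WB-MRI". A lesion seen on either PET but absent on MRI "must be validated by an expert multidisciplinary consensus". The counts by skeletal area follow the same validation rule.

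The Reference Standard section says what the consensus uses. The panel of hematologists, nuclear medicine physicians and radiologists calls each such focus true or false positive "based on patient charts and results from 18-FDG PET/CT, 18F-choline PET/CT, and WB-MRI at baseline". The sentence then adds lesion response to chemotherapy over a 12-month follow-up. It names no imaging modality for that response, no weighting of the inputs and no decision rule.

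Blinding is stated for the image readings. On the PET side, "images will be independently read by two experienced nuclear medicine physicians, blinded from clinical data, biological data, and other imaging data performed during the protocol". On the MRI side, "MRI images will be reviewed by two experienced radiologists blinded from PET/CT, clinical, and biological data". None is stated for the consensus. The Methods describe one choline scan per patient: "patients undergo 3 imaging procedures in the following order: 18F-choline PET/CT, 18-FDG PET/CT, and WB-MRI".

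**The concern.** For a PET-positive, MRI-negative focus, the baseline choline and FDG results are named evidence in the decision that verifies what choline or FDG showed. A focus seen only on choline can therefore be accepted partly because choline showed it. The panel also knows which tracer is being credited, since it holds both results.

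The rule treats the tracers alike, but its effect need not be equal. Relative to a count of MRI-confirmed lesions, the consensus can only add foci, and it adds more to the tracer with more MRI-negative foci. The protocol plans on 75% more foci with choline. The Introduction says that the retrospective study behind this figure had no reference standard. (The sample size section gives the same 75% under a different reference number.) This suggests, without proving, that choline will bring more foci to the panel.

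At stake is the primary conclusion: part of an apparent choline advantage could come from the adjudication rule and not from lesions that exist.

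**Working it through.** **1. The planned figure reproduces.** Inputs from the sample size section: means 10 and 17.5, difference 7.5, SD equal to the mean for each tracer (the text says standard error), correlation 0.85, type I error 5%, power 90%.

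- SD of the paired difference = √(10² + 17.5² − 2 × 0.85 × 10 × 17.5) = √108.75 = 10.43.
- An exact two-sided paired t-test needs n = 23 (power 0.909), the stated number. At n = 30 its power is about 0.97.

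The issue is bias, not sample-size arithmetic.

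**2. What a small excess of accepted foci does when the tracers are equal.** Keep the plan's assumptions, but give both tracers a mean of 10.

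- SD of the paired difference = √(10² + 10² − 2 × 0.85 × 10 × 10) = √30 = 5.48.
- Standard error with 30 patients = √30 / √30 = 1.0 lesion.

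Each net wrongly accepted choline-only focus per patient thus moves the mean difference by about one standard error.

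**3. Simulation of the planned test.** Negative-binomial counts, mean 10 and SD 10 for each tracer, correlation about 0.85, n = 30, no true difference, a Poisson number of wrongly accepted choline-only foci added, two-sided 5% Wilcoxon signed-rank test:

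| Net wrongly accepted choline-only foci per patient | As a share of the planned 7.5 | Trials rejecting |
|---|---|---|
| 0 | 0% | about 4% |
| 0.5 | 7% | about 8% |
| 1 | 13% | about 21% |
| 2 | 27% | about 61% |
| 3 | 40% | about 88% |

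A separate run that counted only significant results in favour of choline gave about 2%, 22%, 60% and 87% for 0, 1, 2 and 3 foci.

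**4. What is assumed.** The excess per patient is an assumption. The article gives neither the share of PET foci that are MRI-negative nor the share of those that a panel would wrongly accept.

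**5. The passages side by side.** The sample size section counts a lesion once it is confirmed on the reference standard, and the Reference Standard section defines that standard as whole-body MRI. The same section and the primary outcome section then admit foci absent on MRI. As written, the primary count can be read as MRI-confirmed lesions only, or as MRI-confirmed plus consensus-accepted lesions.

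**The case against.** A reader might infer that an unblinded panel validates the whole primary count and that choline-only foci will decide the trial. The documents do not support this. MRI read blind to PET comes first, and a choline focus that FDG missed but MRI shows never reaches the panel. With no MRI-negative share given, it is possible but not shown that these foci settle the result. The article does not call the panel unblinded; that it knows the tracer is an inference from its listed inputs.

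A reader might also infer that follow-up cannot help a choline-only focus. That goes too far. Response over 12 months is listed evidence, its modality is open, a site negative at baseline may change on later imaging, and the panel can look again at the MRI. It remains a partial safeguard. Nothing requires such support before acceptance, and the article describes no second choline scan against which response could be judged.

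The panel may also reject foci, which lowers the raw PET counts of either tracer. This stands, but it does not remove the dependence on the index tests. The secondary accuracy analyses against MRI partly cover an MRI-based comparison, though not for the primary count. Masking of the panel may be described in the full protocol. The use of the baseline PET results, however, is a stated rule and not an omitted detail. The statement "The study has been designed to comply with QUADAS 2 guidelines" carries no weight here, because the content of that guideline is not in the documents.

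**Conclusion.** The concern holds for PET-positive, MRI-negative foci. For these, a stated rule makes the index tests part of their own reference standard and feeds the result into the primary count. Any resulting bias favours the tracer with more MRI-negative foci, probably choline on the protocol's own expectation.

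The size is illustrative. It rests on SD equal to the mean, correlation of about 0.85, 30 patients and an assumed excess. Half a wrongly accepted focus per patient does little (about 8% rejection); two, about a quarter of the planned difference, give about 61%. A correlation well above 0.85 would make the inflation larger, but the plan does not assume one. If MRI-negative foci are rare or the panel is strict, the effect is small. This is an improvement to the design that should be made; it does not show the trial to be invalid.

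**What to change.** - In the Reference Standard section, give the panel only the location of each PET-positive, MRI-negative focus. Mask which tracer showed it, and withhold the baseline PET uptake images and readings. The panel judges on an MRI re-look, the CT images separated from the PET uptake, charts and follow-up.
- Count a focus as validated only if evidence other than the index PET uptake supports it.
- Prespecify a repeat of the primary Wilcoxon test on MRI-confirmed lesions only, as a sensitivity analysis.
- Report, per tracer, how many MRI-negative foci were accepted and how many rejected.
- Reconcile the sample size section with the Reference Standard and primary outcome sections, so that it is clear whether MRI-negative foci belong to the primary count.

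The cost is a protocol amendment, masked panel worksheets, the work of separating CT from PET uptake, and one extra analysis. No added scans or patients are needed. The drawback is that some true MRI-negative lesions will not be credited, so the choline gain may look smaller than it is.

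### PET-positive, MRI-negative foci are judged true or false with both index-test results in view, so for this subset the tests under comparison are part of their own reference

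*Protocol article*

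**What the plan says.** The protocol article names WB-MRI as the reference standard and adds a second route for foci that MRI does not show: "Each FL found on 18F-choline or 18-FDG PET/CT and not present on MRI will undergo multidisciplinary consensus". The panel is a "multidisciplinary consensus between hematologists, nuclear medicine physicians, and radiology physicians". It must label each such focus true positive or false positive, "based on patient charts and results from 18-FDG PET/CT, 18F-choline PET/CT, and WB-MRI at baseline". The same sentence then names one further source of evidence: "but also based on lesion response to chemotherapy during a 12-month follow-up".

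Primary Outcome Measures carries this verdict into the endpoint. A lesion that is absent on MRI but "present on any of the PET modalities must be validated by an expert multidisciplinary consensus", and the same rule applies within each of the six skeletal areas. Sample Size Calculation and Statistics then compares the confirmed counts with a Wilcoxon signed-rank test in 30 patients.

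The individual readings are protected. Under Whole-Body MRI, Interpretation Criteria, "MRI images will be reviewed by two experienced radiologists blinded from PET/CT, clinical, and biological data". Both PET sections blind their readers to clinical, biological and other imaging data. Nothing comparable is stated for the panel.

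**The concern.** A reference standard should be settled without the tests it is meant to judge. Here the MRI readings meet that condition and the consensus step does not: the results of both tracers are listed among its inputs. This is a stated rule, not a detail left to a fuller document.

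The verdict on a faint focus that MRI does not show is partly subjective. The panel includes nuclear medicine physicians, and the Discussion (Overview) records the authors' view that "we expect to find that 18F-choline is superior to 18-FDG PET/CT for the detection of bone lesions". If the panel is more lenient or stricter with one tracer, the confirmed counts shift and the primary test reads the shift as a tracer effect. It could go either way. Belief in choline would favour choline-only foci, whereas asking for corroboration by FDG would count against them.

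**Working it through.** **1. Which lesions the panel can affect.** For one patient, let M be the MRI-confirmed lesions seen on a tracer and P the MRI-negative foci on that tracer that the panel accepts. The primary difference is

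D = (M_choline − M_FDG) + (P_choline − P_FDG).

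The first bracket rests on blinded MRI reading. The second rests on the panel. A focus seen on both tracers enters both terms and cancels. The panel can therefore move D only through foci that are MRI-negative and seen on one tracer. The document does not say how many such foci to expect.

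**2. The plan's own figure.** Inputs from Sample Size Calculation and Statistics: mean 10 on FDG, 10 × 1.75 = 17.5 on choline, SD equal to the mean (reading the article's standard error as a standard deviation), correlation 0.85, 5% type I error, 90% power.

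- SD of the difference = √(10² + 17.5² − 2 × 0.85 × 10 × 17.5) = 10.43
- Standardized effect = 7.5 / 10.43 = 0.719
- Two-sided paired t test: n = 23, power 0.909; at n = 30, power 0.968 before any loss from using the Wilcoxon test

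The stated 23 reproduces. The sample size is not in question.

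**3. Scale of the problem with no true difference.** With both means at 10, the SD of the difference is √(100 + 100 − 170) = 5.48, and its standard error with 30 patients is 5.48 / √30 = 1.0 lesion. A net panel error of one lesion per patient is thus about one standard error. It is also 1 / 7.5 = 13% of the planned difference.

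**4. Simulated error rate.** Paired counts, 30 patients, mean 10 and SD about 10 on each tracer, correlation about 0.82 to 0.85, Wilcoxon signed-rank test at 5%. Ranges span repeated simulations. The wrong acceptances are assumptions.

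| Mean wrongly accepted foci per patient, choline / FDG | Rejection rate |
|---|---|
| 0 / 0 | 5.1–5.4% |
| 1 / 1 | 5% |
| 2 / 2 | 4% |
| 0.6 / 0.4 | 6% |
| 1.2 / 0.8 | 8% |
| 0.5 / 0 | 7–9% |
| 1 / 0 | 20–21% |
| 2 / 0 | 54–58% |

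**5. The same question as a gap in acceptance.** Suppose each tracer raises k MRI-negative foci per patient and the panel's acceptance proportion is higher by g for choline. The net shift is k × g. With SD equal to the mean, correlation 0.85 and a paired t test at n = 30:

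| k | g | Net shift | Rejection rate |
|---|---|---|---|
| 2 | 0.1 | 0.2 | 5.4% |
| 3 | 0.2 | 0.6 | 8.7% |
| 5 | 0.2 | 1.0 | 14.9% |
| 5 | 0.3 | 1.5 | 25.9% |
| 5 | 0.5 | 2.5 | 51.7% |

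Both models agree: balanced or mildly unequal errors do little, and a clear imbalance does much. Neither k nor g is in the document.

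**6. What an MRI-only count could show.** If a fraction f of the planned excess of 7.5 is MRI-negative, the MRI-confirmed choline mean is 10 + 7.5 × (1 − f). Paired t power at n = 30 is then 0.954 for f = 10%, 0.901 for 30%, 0.761 for 50% and 0.355 for 75%. An MRI-only run is informative unless most of the excess lies outside MRI.

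**The case against.** Several points on the other side stand.

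- A reader might infer that the panel decides all single-tracer foci, and so the whole contrast. The documents do not support this. A choline-only focus that is present on MRI is confirmed by blinded radiologists and never reaches the panel.
- A reader might take it as stated that the panel knows which tracer raised each focus. It is not stated. It is a reasonable inference, since the panel works from the named results of each tracer and no masking is described, but how cases are presented is something a condensed article may leave to the full protocol.
- The panel has other evidence: charts, MRI and 12-month lesion response, which can overturn a baseline impression. This reduces the concern without removing it, because the modality used to judge response is not named and its independence from PET is not assured.
- Secondary Outcome Measures already plans accuracy for each tracer against MRI and mentions no panel. Against a common set of MRI lesions, the ratio of the two sensitivities equals the ratio of MRI-confirmed counts. Much of the needed check is therefore planned, though not as a test of the primary outcome.
- The rates of 20% and above need one-sided errors. Two net wrong choline foci per patient means 2 × 30 = 60 across the trial.

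One might also hold up the sentence "The study has been designed to comply with QUADAS 2 guidelines" as contradicted. The content of that guideline is not in the document, so nothing here rests on it.

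**Conclusion.** The concern holds for a limited subset. For PET-positive, MRI-negative foci, the results of both index tests are stated inputs to the verdict, and that verdict determines which of these foci count in the primary outcome. MRI-positive lesions are unaffected, and no figure in the plan is wrong.

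Direction and size cannot be derived from the document. Under the assumptions shown, the error rate is about 4% to 8% when wrong acceptances are similar for both tracers, about 20% with an average net excess of one wrong choline-only focus per patient, and 54% to 58% with two. A reader might conclude that the trial's false-positive rate is inflated to the upper figures. That would require a one-sided panel error for which the document gives no evidence.

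This is a cheap improvement and not a must-fix.

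**What to change.** 1. In Reference Standard, have each MRI-negative focus presented to the panel as an anatomical location with MRI, the CT component, charts and follow-up. Withhold the tracer name and the other tracer's baseline result as far as feasible. Allow an indeterminate class beside true and false positive.
2. Pre-specify, as a sensitivity analysis of the primary outcome, the same Wilcoxon signed-rank test on MRI-confirmed lesions only. Also run the full confirmed count with all indeterminate foci taken as false and then all as true, and name in advance which of these two is the primary count. This complements the accuracy analyses against MRI already planned.

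The MRI-only result should inform how the primary result is read. Making a superiority claim depend on it is a debatable trade-off and is not proposed, since true lesions that MRI misses would then not count.

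The cost is a masked case sheet and two further runs of the same test, with no new scan or reader. The article reports 8 of 30 patients included by June 2020, and verdicts draw on 12-month follow-up, so at that date masking was still feasible for most patients. The drawbacks are that the panel decides on slightly less information, some foci stay indeterminate, and masking may be incomplete if follow-up itself uses PET.
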